# Nutrition and physical activity intervention for families with familial hypercholesterolaemia: protocol for a pilot randomised controlled feasibility study

**DOI:** 10.1186/s40814-020-00584-3

**Published:** 2020-04-02

**Keywords:** Familial hypercholesterolaemia, Diet, Physical activity, Cardiovascular disease, Intervention, Dietetics, Paediatrics, Primary prevention, Qualitative, Feasibility

## Abstract

**Background:**

Untreated heterozygous familial hypercholesterolaemia (FH) causes high low-density lipoprotein cholesterol (LDL-C) levels and increased cardiovascular disease (CVD) risk. Despite pharmacological treatment, many treated individuals remain at higher CVD risk than non-affected individuals. This may be due to LDL-C targets not being met and presence of other CVD risk factors. Adhering to dietary and physical activity (PA) recommendations developed for individuals with FH may further reduce CVD risk. However, there is insufficient research to support the efficacy of adhering to these guidelines on LDL-C and other CVD risk factors. The need for studies to investigate the effectiveness of nutrition and PA interventions in the FH population has been widely recognised and recommended. This paper describes the protocol of a pilot, randomised controlled trial designed to evaluate the feasibility and acceptability of a specifically developed nutrition and PA intervention aimed at improving the dietary intakes and PA levels of families with FH.

**Methods:**

A two-arm randomised waitlist-controlled pilot trial will be conducted across three National Health Service (NHS) sites in England, UK. Twenty-four young people with FH, aged 10–18 years, and their affected parent, will be recruited and randomly assigned to the intervention or waitlist and usual care control. The primary aim is to provide evidence for the feasibility and acceptability of delivering the intervention, explored quantitatively (rates of recruitment, retention and outcome measure completeness) and qualitatively (qualitative interviews). The secondary aim is to provide evidence for the potential efficacy of the intervention on dietary intake, PA, sedentary time, body composition, CVD risk factors and quality of life determined at baseline and endpoint assessments. The intervention will involve an hour-long consultation with a dietitian at baseline and four follow-up contacts across the 12-week intervention. It has been specifically developed for use with individuals with FH and incorporates behavioural change techniques to target identified enablers and barriers to adherence in this population.

**Discussion:**

This trial will estimate the feasibility and acceptability of the nutrition and PA intervention delivered to young people and parents with FH. If appropriate, this study can be used to inform the design of an adequately powered definitive trial.

**Trial registration:**

ISRCTN, ISRCTN24880714. Registered 07/06/2018, http://www.isrctn.com/ISRCTN24880714.

## Background

Heterozygous familial hypercholesterolaemia (FH) is an autosomal dominant hereditary disorder, characterised by markedly elevated levels of low-density lipoprotein cholesterol (LDL-C) from birth [1]. The lifelong exposure to elevated LDL-C levels confers a substantially increased risk of premature cardiovascular disease (CVD) and associated mortality [2] to the 1 in 250 people affected worldwide [3]. While the introduction of pharmacological treatment has dramatically reduced the incidence of CVD in individuals with FH, they remain at increased risk [4–7]. The residual CVD risk may be attributed to the large number of adults and young people that do not reach LDL-C treatment targets, even on maximally tolerated doses [8, 9]. Additionally, the presence of other risk factors such as hypertension, obesity and type II diabetes have been shown to be independently associated with their CVD risk [6, 10–14]. Efforts are currently focussed on improving the low overall detection of this disorder, which is estimated to be identifying only 1–15% of those at risk worldwide [15]. It is therefore crucial to optimise the treatment provided to this rapidly increasing vulnerable patient population group.

Lifestyle advice is considered an important adjuvant to pharmacological treatment for individuals with FH. All individuals are recommended to receive individualised advice about diet, physical activity and the maintenance of a healthy weight from a healthcare professional (HCP) with specific expertise [16–18]. Dietary and physical activity recommendations are based on the same principles as advised for the general population, with additional emphasis to reduce intakes of foods high in fat, saturated fat and cholesterol and to consume foods with LDL-C-lowering effects such as plant phytosterols/phytostanol s[16–18].. Despite these recommendations, comprehensive systematic reviews have concluded that there is insufficient data to make any conclusions about the effectiveness of any dietary or physical activity intervention upon CVD risk or surrogate outcomes in adults or young people with FH [19, 20]. Extrapolating the results of such interventions carried out in other patient populations is inappropriate as this does not allow for consideration of the unique physiological and psychological factors present in individuals with FH. Randomised controlled trials (RCTs) to investigate the effectiveness of dietary and physical activity interventions within FH cohorts have been recommended to address this research gap [18–21].

An understanding of how and why individuals with FH display certain behaviours and an awareness of the factors influencing their decisions to adhere to treatment should be considered in the development of an intervention. Adherence to lifestyle recommendations in affected individuals is sub-optimal whereby less than 50% of adults reported following the recommended lifestyle advice [22]. Additionally, overweight and obesity has been reported in cohorts of adults and young people with FH, suggesting that the advice is not being followed by all [9, 14, 23]. Given the chronic nature of FH, it is essential that an intervention enables individuals to make lifelong behavioural changes, rather than for the short duration of a clinical trial. As the greatest reduction in CVD risk is achieved when treatment is started at a young age [4, 24], young people stand to gain the most for receiving a lifestyle intervention. Given the increasing diagnostic rates and high prevalence of FH, any intervention to be evaluated should also be pragmatic and feasible to provide within the constraints of current healthcare services.

In the current research, we propose to develop and evaluate a family-based nutritional and physical activity intervention to enable young people with FH, and their affected parent, to achieve dietary and physical activity recommendations thus reducing their CVD risk. As there is currently insufficient evidence to support a large, full-scale RCT to evaluate such an intervention, a pilot RCT is needed as advised in the British Medical Research Council (MRC) framework for the development and evaluation of complex interventions [25, 26].

### Study aims and objectives

The primary aim of this study is to provide evidence for the feasibility and acceptability of conducting a future adequately powered, randomised controlled trial to evaluate a specifically designed nutrition and physical activity intervention in young people and their affected parent with FH. The primary objectives of the study are to explore the following questions:
Will young people and their parent be willing to participate in the proposed family-based intervention?Will families accept randomisation to the control or intervention group, adhere to research methods in their allocated group and complete the study?Are the research methods that are used to capture data fit for purpose?Is there sufficient protocol fidelity in the intervention group?Upon completion of the study, was the overall experience of the intervention and/or the study research processes positive and potentially reproducible in an adequately powered trial?

The secondary aim of this study is to estimate the potential efficacy of the intervention on the dietary intake, physical activity and sedentary time, body composition, selected CVD risk factors and quality of life of young people and their affected parent with FH.

## Methods

This protocol is reported in accordance with SPIRIT (Standard Protocol Items: Recommendations for Interventional Trials) guidance and a completed checklist is available in Additional File 1.

### Study design and setting

This pilot study is a two-arm, randomised waitlist-controlled trial comparing a specifically developed nutrition and physical activity intervention against usual-care waitlist control amongst young people with FH. This study aims to recruit family units, each comprised of a young person-parent dyad. This is in recognition of the autosomal dominant presentation of FH which means all affected young people will have one affected parent. This will also facilitate the proposed family-based delivery of the intervention. This study will be conducted across three National Health Service (NHS) Foundation Trust sites in England, UK: University Hospitals Bristol, Royal United Hospitals Bath and St. George’s University Hospitals London (Fig. 1).

**Fig. 1 Fig1:**
[figure not shown]
Study flow diagram

### Study population

In this family-based intervention, young person(s) aged 10–18 years and their affected parent with FH will be invited to participate. A family unit will be comprised of at least one adult and one young person with FH, but there may also be family units in which additional young family members with FH take part.

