### Sample size

This is an exploratory feasibility study and therefore no power calculation has been used to determine sample size because it is not designed or powered to address the effectiveness of the intervention being evaluated [25, 27, 28]. Sample sizes of between 24 and 50 have been recommended for feasibility studies wishing to provide a standard deviation estimation to inform the sample size calculation of a larger RCT [27, 29, 30]. The target sample size of 24 family units in this study has been based upon this recommendation in addition to knowledge of the current local FH population.

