### Randomisation and blinding

Randomisation, stratified by study site, will allocate family units to either usual care and waitlist (control) or to the nutrition and physical activity intervention (intervention) on a 1:1 basis. To facilitate recruitment and retention, family units allocated to the control arm will be placed on a waitlist to receive the intervention at the end of the 12-week study period. Randomisation will be carried out by an independent person using prepared, password-protected randomised lists, following obtainment of informed consent to participate. Family units will be notified of their assigned group at research visit two, after baseline data collection. Due to the nature of the intervention, delivery and study design, it is not possible to blind participants, clinical staff or research staff to the randomisation results. Upon completion of the study, participants in the control group will be asked if they had any communication with other young person-parent dyads in the study. This will assess potential intervention contamination bias which will be taken into consideration in the analysis. The anticipated likelihood of this occurring is low due to the infrequency of outpatient appointments (usually once a year) that families attend.

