### Analysis plan

Data collected from young people will be analysed separately from the data collected for adult parent participants.

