#### Quantitative data

Recruitment, randomisation and retention rates, attendance at study visits, completion rates of questionnaires, completeness of dietary intake and physical activity data, rates of successful collection of clinical measurements and categorisation results of self-reported physical activity levels will be descriptively analysed. The other quantitative variables of interest (Table 1) are continuous. Therefore, where possible, groups will be summarised by means and standard deviations (S.D.) for (i) baseline, (ii) end point assessment and (iii) for the changes over the intervention period. This will be carried out for individuals in the control and intervention groups.

Comparisons will be made between the endpoint assessment means in the intervention and control groups with or without adjustment for the baseline values and stratification, as appropriate. 95% confidence intervals (C.I.) will be reported for mean differences. Comparisons may be made between the intervention and control groups in respect of the mean changes from baseline if this is found to improve precision [82].

Additionally, the dietary intake and physical activity data at both baseline and endpoint assessment will be compared to the target levels determined for the intervention (outlined previously in ‘intervention content’) and will be descriptively analysed for participants in the control and intervention groups.

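### If siblings enrol, the young people's 95% CIs will tend to be too narrow: families are randomised, but the stated comparison makes no allowance for family

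*Protocol article*

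**What the plan says.** Under Randomisation and blinding, the unit of allocation is the family: "Randomisation, stratified by study site, will allocate family units", in a 1:1 ratio. Under Sample size, the target is also counted in families: "The target sample size of 24 family units in this study has been based upon this recommendation", and "no power calculation has been used to determine sample size".

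Study population allows more than one child in a unit: "there may also be family units in which additional young family members with FH take part".

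The Analysis plan separates the generations: "Data collected from young people will be analysed separately from the data collected for adult parent participants". Its Quantitative data subsection describes means and SDs at baseline, at endpoint and for change, and closes that paragraph with "This will be carried out for individuals in the control and intervention groups". The next paragraph compares endpoint means between arms "with or without adjustment for the baseline values and stratification, as appropriate", with 95% CIs for the mean differences. The stratification factor is study site.

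The article mentions no family term, cluster-robust standard error, family mean or index child. The one link between participants that it plans to take into account is contamination between dyads.

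**The concern.** Randomising families makes this a small cluster-randomised comparison wherever a family contributes more than one person to an analysis set. Analysing adults and young people separately deals with the parent–child pair and normally leaves one adult per family. It does not deal with siblings. They are always in the same arm and share a household and an inherited disorder. In the intervention arm they also share the dietitian session, since delivery is to the family. For diet, activity and lipid outcomes a positive correlation is to be expected.

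If the comparison is run as written, each sibling counts as a full extra observation. The standard error of the young people's mean difference is then understated and the interval covers less often than 95%. At stake is the precision claimed for the secondary estimates of potential efficacy.

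**Working it through.** **No figure to reproduce.** The target of 24 families comes from a rule of thumb (24 to 50) and local knowledge, not from a power calculation.

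**Inputs from the article.** 24 family units, 1:1, so 12 per arm; siblings allowed; two-sided 95% CIs; adjustment named only for baseline and stratification.

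**Assumed, because the article does not give them.** k = number of families with two participating siblings (all others have one young person), and the ICC between siblings.

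**Formulas.** With m the number of young people in a family and N = Σm:
- design effect DEFF = 1 + (Σm²/N − 1) × ICC
- true SE ÷ SE ignoring family = √DEFF
- approximate coverage of the nominal 95% CI = 2Φ(1.96/√DEFF) − 1

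For k=6: N = 18 + 12 = 30 and Σm² = 18 + 24 = 42. So DEFF = 1 + 0.4 × 0.5 = 1.20 at ICC 0.5, and √1.20 = 1.095.

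| k | N | Σm² | ICC | DEFF | SE ratio | Coverage |
|---|---|---|---|---|---|---|
| 0 | 24 | 24 | any | 1.00 | 1.00 | 95.0% |
| 2 | 26 | 30 | 0.3 | 1.046 | 1.023 | 94.5% |
| 4 | 28 | 36 | 0.3 | 1.086 | 1.042 | 94.0% |
| 6 | 30 | 42 | 0.5 | 1.200 | 1.095 | 92.6% |
| 10 | 34 | 54 | 0.7 | 1.412 | 1.188 | 90.1% |

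Simulation of the two-sample t interval that ignores family agrees: 94.6% (k=2, ICC 0.3), 94.0–94.2% (k=4, ICC 0.3), 92.6–92.7% (k=6, ICC 0.5) and 89.6–89.8% (k=10, ICC 0.7).

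**Interval width at k=6, ICC 0.5.** Ignoring family, the half-width is t(28 df) × √(4/30) = 2.048 × 0.365 = 0.75 SD. With family clustering and 22 df it is 2.074 × 0.365 × 1.095 = 0.83 SD. The SE ignoring family is about 9% too small (1 − 1/1.095).

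**Effect on the SD.** Within an arm of n young people, the expected sample variance is σ²[1 − ICC × Σm(m−1)/(n(n−1))]. With sibling families split evenly between arms:
- k=4, ICC 0.3: 0.3 × 4/(14×13) = 0.0066, so the SD is low by about 0.3%
- k=6, ICC 0.5: 0.5 × 6/(15×14) = 0.0143, about 0.7%
- k=10, ICC 0.7: 0.7 × 10/(17×16) = 0.0257, about 1.3%

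**Precision of an ICC from six pairs.** On Fisher's scale with SE 1/√(6 − 1.5) = 0.471, an observed 0.5 gives 0.549 ± 0.924, that is, about −0.36 to 0.90.

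**The case against.** The strongest reply is that the article nowhere says that observations will be treated as independent. The sentence about individuals closes the descriptive paragraph. The comparison paragraph names no model, test or standard-error method, and a random intercept is a detail that a SAP could supply. This stands in part: independence is inferred. But the article does state a comparison and lists its adjustments, and that list does not match the unit it randomises. Followed as written, the plan ignores sibling clustering.

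The second reply is that the design is built on dyads. Siblings are only a possibility, and the Abstract counts twenty-four young people, the same number as the families. This stands. A reader might infer that the CIs are bound to be too narrow, but the article does not support that: with no sibling pairs there is no effect, and with one or two it is small. The values k=6 and k=10 are illustrations without a source in the article.

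Third, the article allows baseline adjustment. The ICC that then matters is that of the adjusted residuals, and it may be lower because stable household habits and the shared variant are partly absorbed. The shared session acts only in the intervention arm during the 12 weeks. This also stands and points to the milder end of the range.

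Finally, the affected intervals are secondary and exploratory. That is correct and limits the weight of the point.

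**Conclusion.** The point holds in conditional form. The randomised unit is the family, a family may contribute several young people, and the stated comparison adjusts for nothing beyond baseline and stratification. If siblings enrol with positively correlated outcomes, the young people's 95% CIs will be too narrow. Across the assumed scenarios, coverage runs from 95% (no siblings) to about 90% (ten sibling families, ICC 0.7), with about 92.6% in the middle case.

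Two stronger readings are not supported. One is that the SD passed to a future trial is compromised: its bias is about 1% or less in all but the most extreme scenario, where it is 1.3%, which is trivial beside the sampling error of an SD from about 30 young people. The other is that the trial's main conclusions are at risk: recruitment, retention, completeness and interview findings are largely unaffected. This is a unit-of-analysis mismatch with a modest effect on secondary results.

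**What to change.** In the Quantitative data part of the Analysis plan, state that the family is the unit of inference for the young people's comparisons. Fit the baseline- and site-adjusted model with a family random intercept and small-sample degrees of freedom (for example Satterthwaite). If that model does not fit, which is possible with few sibling pairs, analyse family means.

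Report the number of families and the number of young people per arm. If a within-family correlation is reported, give its CI and say that it is too imprecise to plan with on its own.

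The cost is a few lines of analysis wording and slightly wider CIs. Recruitment, data collection and conduct do not change, so the fix remains possible although data collection is complete. If no siblings took part, one sentence saying so is enough.

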#### Eligibility criteria

Individuals aged 10–18 years with a genetically confirmed clinical diagnosis of heterozygous FH who receive their care from the paediatric or adult lipid clinics at the three NHS Foundation Trust sites will be invited to join the study. Their parent (≥ 18 years), with a genetically confirmed clinical diagnosis of heterozygous FH, will also be invited to join the study.

Pregnant female patients, or those planning pregnancy, and individuals who are unable to give informed consent or assent for those aged 10–15 years are not eligible for participation. Patients with a diagnosis of homozygous FH and patients not established on their current treatment regimen for at least 1 month prior to recruitment to the study are not eligible for participation.

If a young person with FH wishes to join the study but their affected parent is deceased or does not want, or is not eligible to participate, then the young person will still be able to participate. In this instance, a non-affected parent or main carer of the young person will be invited to take part to facilitate the family-based aspect of the study if they wish. However, blood samples will not be collected from these non-affected participants. In instances where the non-affected parent or main carer also does not wish to take part, the young person with FH will still be able to participate on their own.

### Recruitment

#### Identification

All young people receiving care from paediatric or adult lipid clinic services at participating sites will be screened for eligibility. The eligibility of their affected parent will then be considered. This will be carried out by a member of the hospital care team and will be repeated every 3 months during the recruitment phrase. This will be conducted at both paediatric and adult clinics because young adults often transition to adult services before the age of 18 years.

#### Invitation to participate

A study invitation letter and an age-appropriate participant information sheet (PIS) will be sent to the families of young people who are identified and deemed to meet the inclusion criteria from review of medical records. A PIS will also be included for the parent of the identified young person. Contact details of the research team are provided in this PIS and families interested in participation are asked to make contact. The study will also be described, and a PIS provided, to young people and their parent(s) attending either paediatric or adult lipid clinics. For families expressing an interest in participation, a meeting or phone call will be arranged with a member of the research team.

### Sample size

This is an exploratory feasibility study and therefore no power calculation has been used to determine sample size because it is not designed or powered to address the effectiveness of the intervention being evaluated [25, 27, 28]. Sample sizes of between 24 and 50 have been recommended for feasibility studies wishing to provide a standard deviation estimation to inform the sample size calculation of a larger RCT [27, 29, 30]. The target sample size of 24 family units in this study has been based upon this recommendation in addition to knowledge of the current local FH population.

